## 3. Outcome Measures and Measurement Procedures

The assessment of physical functions will be carried out by two physiotherapists experienced in the management of patients with dementia, whilst the neuropsychological evaluation will be performed by a neuropsychologist or psychologist of the center. All assessors who will participate in data collection will be trained in study procedures prior to the study.

The primary objective of the study is to determine the effects of exercise on the cognitive function and functionality of persons suffering from mild Alzheimer’s disease. Addenbrooke’s Cognitive Examination—Revisited (ACE-R), Mini Mental State Examination (MMSE), Trail Making Test A (TMT-A), Trail Making Test B (TMT-B), Digit Span Test Forward and Backward (DST F-B) were selected for the evaluation of cognitive function. The Senior Fitness Test (SFT), Berg Balance Scale (BBS), and Instrumental Activities of Daily Living Scale (IADL) were selected for the functionality evaluation.

The secondary aim of the study is to determine the effect of exercise on an individual’s mood, for which the Geriatric Depression Scale-15 (GDS-15) was chosen, as well as the effect of exercise on physical activity by using the International Physical Activity Questionnaire (IPA-Q) short edition—7 items, as well as compliance with the intervention.

All assessment tools have been proven valid and reliable in Greek and have been widely used in studies involving elderly and dementia patients [17,18,19,20,21,22,23,24,25,26,27].

### 3.1. Description of Outcome Measures

#### 3.1.1. Assessment of Cognitive Functioning and Mood

##### Addenbrooke’s Cognitive Examination Revised

The ACE-R is a brief cognitive assessment tool [17]. The ACE-R takes between 12 and 20 min (16 on average) [28]. It contains five subscales, each of which represents a cognitive domain: (a) attention/orientation (18 points), (b) memory (26 points), (c) verbal fluency (14 points), (d) language (26 points), and (e) visuospatial ability (16 points) [17,28]. The maximum ACE-R score is 100, consisting of the addition of all domains indicating better cognitive function [17,28].

##### Mini Mental State Examination

The MMSE is the most widely used assessment tool for diagnosing cognitive disorders. Its administration procedure is simple and takes 5 to 10 min [18,29]. The MMSE consists of tests (30 sub questions) which examine five cognitive domains: (a) orientation, (b) attention–concentration, (c) memory, (d) language, and (e) visuospatial ability [30]. For each correct answer, we obtain one point, and for each wrong one, zero points, with a maximum performance in the test of 30 points [29,30,31]. Higher performance indicates better cognitive functioning [29,30,31].

##### Trail Making Test A–B

The TMT is an easy and quick neuropsychological test; it assesses cognitive abilities such as attention, processing speed, and executive functions [32]. The TMT consists of two parts in which the examinee is instructed to connect a set of 25 dots as quickly as possible while maintaining accuracy [19,32]. In the first part (TMT-A), the targets are all numbers (1, 2, 3, etc.) and the examinee must connect them in consecutive order [19,32]. In the second part (TMT-B), the subject alternates between numbers and letters (1, A, 2, B, etc.) [19,32]. The aim of the test is for the assessee to complete both parts as quickly as possible [19]. The test of each part ends after 5 min even if it is not completed [32].

##### Digit Span test

One of the most common tests for assessing attention and working memory is the Digit Span Test [33,34]. With the DST, recent memory is assessed [34]. The score is the sum of the number of digits from the forward repetition in which the examinee is asked to repeat after the examiner (DST-F) and the number of digits from the reverse repetition (DST-B) [33,34]. The test is terminated when the subject does not accurately record the trial in a sequence length or when the maximum list length is reached [33,34]. The total number of subtests (DST F-B) are summed to produce a total score [33]. Scoring is conducted with two points if the examinee repeats both series correctly at the particular difficulty level under consideration, with one point if they repeat one series correctly, and with zero points if they fail both [34].

##### Geriatric Depression Scale-15

The GDS-15 is a short-form self-report test of 15 questions [25,35,36,37]. The GDS-15 is a widely used scale internationally [25]. The 15 questions of the short form of the scale require only a YES–NO answer and take approximately 5–7 min [25]. The questionnaire is completed with an interview [35,36,37]. Each answer of the test is scored 0 or 1 [25,38]. In questions 1, 5, 7, 11, 13, the answer “NO” is scored with 1 point, while in the remaining questions, the answer “YES” is scored with 1 point [25,38]. For the severity of depression, the following categorization is followed: 0–5 points correspond to “absence of depressive symptoms”, 6–10 to “moderate depression”, and 11–15 to “severe depression” [25,38].

#### 3.1.2. Functional Fitness Assessment

##### Senior Fitness Test

The SFT is a practical set of tests for clinical use and is suitable for both healthy seniors and people with dementia and is simple to use [39,40]. It is an international easy-to-use tool for measuring functional fitness in older people with or without cognitive impairment and is suitable for both research and clinical purposes [21,39,40,41]. It is simple to use, requires no expensive tools or technical expertise, and can be performed in any location [40,42,43,44,45]. The test includes six functional tests of arm and leg strength, endurance, balance, agility, and flexibility and takes approximately 30–40 min to complete [41,42,43]. The Senior Fitness Test was modified and adapted to Greek data. During the Arm Curl test, weights of 2 kg and 3.5 kg will be used, for women and men, respectively, and flexibility will be measured in centimeters [41,44,45,46,47].

##### Berg Balance Scale

The BBS is a popular and well-established clinical tool for assessing balance [22]. It is known as a balance measurement tool in the elderly but has also been tested for its reliability and validity in assessing balance in patients with various neurological diseases with very good results [22]. The BBS assesses the subjects’ static and dynamic balance ability and predicts the likelihood of falls by performing simple tests that require good balance [22,48]. It consists of 14 simple tests, which are often performed in daily activities and is mainly used to assess people with mobility difficulties such as the elderly [48]. The time required to complete all tests is 15–20 min [22,49]. Test takers are scored on a scale of 0–4 based on their ability to perform the required tests [22,49]. The total score ranges from 0 to 56 and a score of less than 45 equates to an increased risk of falls [22,49]. Higher scores indicate better performance and greater independence [22,49]. A cut-off point of 45/56 has been suggested for independent and safe movement [22,49]. It is an easy and quick physical performance test that requires no training or special equipment [22].

##### Instrumental Activities of Daily Living Scale

The IADL was first presented in 1969 by Lawton and Brody [50]. The IADL questionnaire explores individuals’ basic ability to care for themselves and refers to higher levels of performance [23,24,50,51]. The present questionnaire is a suitable tool for assessing independent living skills in both healthy elderly and elderly patients with dementia and mild cognitive impairment [23,24,50,51,52]. The questionnaire is completed with an interview [51]. The IADL is an assessment tool, easy to administer, and administration time is 10–15 min [51]. The IADL questionnaire scale measures eight domains of functioning: telephone use, shopping, food preparation, housekeeping, laundry, mode of transportation, responsibility for personal medication, and ability to manage finances [23,50,51]. Women are rated in all 8 functional areas [23]. Men are excluded from the areas of food preparation, cleaning, and laundry [23]. Each domain is scored 0 or 1, respectively, when respondents report difficulty, or receive help with the task, or could not perform the task [23,50,51]. The total score ranges from 0 (low functioning, dependent) to 8 (high functioning, independent) for women and 0 to 5 for men [23,50,51].

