## 5. Statistical Analysis

Descriptive and inferential statistical analysis will be carried out. The normality of the variables under consideration will be tested with the Shapiro–Wilk test. Possible dependencies between qualitative variables and categorical scales characteristics of the three different groups will be investigated using Pearson’s chi-squared test (χ^2^).

A paired t-test or the non-parametric Wilcoxon signed-rank test was performed to analyze whether there was any significant improvement in the cognitive function and mood (ACE-R, MMSE, TMT A-B, DST F-B, and GDS-15) and functionality (SFT, BBS, IADL, and IPAQ) after the subjects had completed the 12 weeks intervention of the two different exercise programs.

In order to investigate differences between groups, at baseline and after the intervention, one-way ANOVA F-tests, or Kruskal–Wallis tests for more than two independent samples will be carried out for all the mentioned variables, both at baseline and after the intervention (12 weeks). Bonferroni correction was applied to adjust for multiple pair-wise comparisons of the means for the main effects.

Pearson’s or Spearman’s correlation tests for the total changes from baseline will be applied accordingly to normality test. Variables correlated significantly will be used for further multivariate analysis. To further analyze the relationship between the changes of outcome measures, a multivariate linear regression analysis will also be applied for the total changes from baseline, in order to clarify the effect of exercise in cognitive function and functional performance. If group differences are observed at baseline, those variables are included as covariates in further analyses. To assess the effect on the primary and secondary outcome measures, analysis of covariance (ANCOVA) is used with cognitive domain scores on the post-tests as dependent variables, pre-test scores as covariates, and group (combined aerobic and resistance exercise program, single resistance exercise program, control) as the between-subject factor.

Statistical analyses will be carried out using the statistical software package SPSS 24.0 for Windows (SPSS Inc., Chicago, IL, USA). *p*-values less than 0.05 are considered statistically significant.

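### IADL is scored 0–8 in women and 0–5 in men but tested as one raw variable, so the pooled arm difference has no single meaning and the 12-week comparison loses some power

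*Protocol article*

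**What the plan says.** Section 3 (Outcome Measures and Measurement Procedures) sets the objective: "The primary objective of the study is to determine the effects of exercise on the cognitive function and functionality of persons suffering from mild Alzheimer’s". It then lists the functionality measures: "The Senior Fitness Test (SFT), Berg Balance Scale (BBS), and Instrumental Activities of Daily Living Scale (IADL) were selected for the functionality evaluation". IADL is thus one of several measures under the primary objective.

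The IADL description in section 3.1.2 scores women on eight domains, while "Men are excluded from the areas of food preparation, cleaning, and laundry". The consequence is stated there: "The total score ranges from 0 (low functioning, dependent) to 8 (high functioning, independent) for women and 0 to 5 for men".

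Section 5 (Statistical Analysis) treats IADL in up to three ways:

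- It is named among the variables for the paired t-test or Wilcoxon signed-rank test of change over 12 weeks.
- It falls under the between-group tests: "Kruskal–Wallis tests for more than two independent samples will be carried out for all the mentioned variables, both at baseline and after the intervention (12".
- It may fall under the ANCOVA. That sentence opens by referring to the primary and secondary outcome measures, and then specifies: "analysis of covariance (ANCOVA) is used with cognitive domain scores on the post-tests as dependent variables, pre-test scores as covariates".

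One further rule bears on the point: "If group differences are observed at baseline, those variables are included as covariates in further analyses". No step puts the two sexes on one scale, and section 2.4 describes allocation by random number generator without mention of stratification by sex.

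**The concern.** The raw total does not measure the same thing in the two sexes. The best possible score is 5 for a man and 8 for a woman, so part of the spread in the pooled variable comes from the scoring rule and not from function. Ranking does not remove this: a man at 5 of 5 is ranked below a woman at 6 of 8 and tied with a woman at 5 of 8. A mean difference of one raw point also has no single interpretation, since it is 1/8 of the scale for a woman and 1/5 for a man.

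Two things are at stake. The sex gap adds to the error variance of the 12-week comparison and so costs power. And when the arms differ by chance in their sex mix, that imbalance appears as a difference in IADL although function is the same.

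**Working it through.** **Inputs from the article.** Score ranges 0–8 and 0–5 (section 3.1.2). Alpha 0.05, power 80%, f = 0.23–0.24, 171–186 participants, 57–62 per group (section 2.2).

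**Inputs assumed.** The article gives no sex ratio and no IADL distribution. Base case: 60% women, a share p = 0.6 of applicable activities performed, beta-binomial scores with precision 4 (between-item correlation 1/(4+1) = 0.2), 60 per arm. Ranges: men 30–50%, p = 0.4–0.8, correlation 0–0.4.

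**1. The plan's own figure.** One-way ANOVA, noncentral F with λ = N·f², 2 and N − 3 degrees of freedom: f = 0.24 gives N = 171 (power 0.802) and f = 0.23 gives N = 186 (power 0.802). The stated range reproduces.

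**2. Gap due to scoring alone.** At equal relative function, women minus men = 8p − 5p = 3p. At p = 0.6 this is 4.8 − 3.0 = 1.8 points; at p = 0.5–0.7 it is 1.5–2.1 points.

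**3. Variance cost, closed form.** In the base case:

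- Between-sex variance: 0.6 × 0.4 × 1.8² = 0.78.
- Within-sex variance, k·p(1 − p)·[1 + (k − 1)·0.2]: women 8 × 0.24 × 2.4 = 4.61; men 5 × 0.24 × 1.8 = 2.16; weighted 0.6 × 4.61 + 0.4 × 2.16 = 3.63.
- Share due to sex: 0.78 / (0.78 + 3.63) = 0.176.
- If f = 0.23 holds on a sex-comparable scale, then on the raw score f = 0.23 × √(1 − 0.176) = 0.209, and power at N = 186 falls from 0.80 to about 0.72. Over the full assumed range it is 0.42–0.78.

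**4. How often sex mix differs.** With 60 per arm and 60% women, exact binomial: a given pair of arms differs by at least 10 percentage points in 30.5% of randomisations and by at least 20 points in 3.2%.

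**5. Shift when it does.** Shift = imbalance × gap. For 10 points, 0.10 × 1.8 = 0.18; for 20 points, 0.20 × 1.8 = 0.36 raw points with no difference in function.

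**6. Simulation of a two-arm comparison, base case.** The effect is a gain of 0.12 in the share of activities kept.

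| Analysis | Power | Type I error, 20-point imbalance | Shift, 20-point imbalance |
|---|---|---|---|
| Raw 12-week score | 53% | about 13% | 0.36 |
| Percentage, 12-week | 63% | 5% | 0 |
| Raw, ANCOVA with baseline | 82% | 6–7% | 0.11 |
| Percentage, ANCOVA with baseline | 83% | 5% | 0 |

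Averaged over randomisations, type I error of the raw 12-week test is about 5%. Given a 10-point imbalance it is about 5.7%. The raw change score shows no shift and 5% type I error even under a 20-point imbalance.

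**7. Three-arm simulation under a different model** (62 per arm, 40% men, about 57% of activities performed): 12-week ANOVA power 0.50 raw against 0.59 as a percentage. With the baseline covariate it is 0.725 raw, 0.749 with sex added and 0.736 as a percentage. At about 73% of activities performed, the three ANCOVAs give 0.625, 0.666 and 0.664. The loss after baseline adjustment is therefore about 1–4 points.

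**The case against.** **The ANCOVA may already cover IADL.** A reader might infer that ANCOVA is planned for cognitive scores only, which would leave IADL without baseline adjustment. The text does not support that as a fact: the sentence opens with the primary and secondary outcome measures, and IADL is among the primary ones. It then names only cognitive scores as the dependent variable, so coverage is ambiguous. If IADL is covered, the baseline score carries most of the sex difference and the problem becomes small. This stands, and it limits the size of the point.

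**Conditional covariates.** The rule for adding variables that differ at baseline could bring in sex, since qualitative characteristics are compared by chi-squared. With 60 per arm and a 20-point gap between two arms, that test gives p = 0.03–0.04 if the third arm matches either extreme and p = 0.08 if it lies midway. The rule therefore catches some imbalances and misses others, and it recovers no power when the arms are balanced.

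**Paired tests.** A reader might count these as distorted by sex mix. They are not: each person is compared with himself or herself. Only the unequal unit of change remains.

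**Condensed article.** The scoring comes from cited sources, and a fuller plan may rescale the score. That is possible and lowers certainty. But the article states both the scoring rule and the tests applied to the score, and as written the two do not fit.

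**Conclusion.** The point holds in a limited form. As written, the plan pools two scales that are not comparable for a measure under the primary objective. The ranking anomaly and the unequal unit (12.5% against 20%) follow from the article alone and need no assumption.

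A reader might go further and infer a biased test with inflated error. That is not supported: under randomisation there is no bias on average and type I error stays near 5%. The figure of about 13% is conditional on a 20-point sex imbalance, which arises in about 3% of randomisations for a given pair of arms.

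The everyday cost is power: about 10 points in the unadjusted 12-week comparison (53% against 63%), falling to about 1–4 points if the baseline-adjusted ANCOVA is the test used. All power, error and shift figures rest on an assumed sex ratio and IADL distribution and are illustrative. The change is worth making, but one outcome among several is affected and the validity of the trial is not in question.

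**What to change.** Before the data are analysed, state four things:

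1. IADL is analysed as the percentage of applicable activities (score/8 for women, score/5 for men) or, alternatively, as the total of the five domains scored in both sexes.
2. The same formula is used at baseline and at 12 weeks.
3. The between-arm test is an ANCOVA with baseline IADL and sex as prespecified covariates, whatever the baseline comparison shows.
4. The ANCOVA covers the functionality outcomes as well as the cognitive ones.

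This takes a line or two in the analysis plan, with no new data and no change in trial conduct. The small cost is that the result is no longer on the familiar 0–8 scale; raw totals can still be described separately for women and men.

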##### International Physical Activity Questionnaire (Short Edition—7 Items)

The IPAQ was developed as a means to monitor and assess physical activity and inactivity for all ages, including the elderly [53,54,55]. In our study, we will use the IPAQ—GR (short version—7 items) which consists of seven questions which participants are asked to answer in order to determine the number of days and minutes per day they spend on either vigorous or moderate physical activity, how much time they spent walking over the past seven days as well as sitting down during a typical week [26,27]. The questionnaire is completed by means of an interview [26]. The activity withdrawal period concerns the previous seven days [26,27].

According to IPAQ scoring, the physical activity is categorized as follows: (a) low physical activity, (b) moderate physical activity, and (c) high physical activity [26].

## 4. Therapeutic Intervention

The intervention will include aerobic as well as resistance exercise. For this purpose, three groups will be created, two (2) intervention groups and one (1) control group. The first intervention group will follow a program containing both aerobic and resistance exercise and the second group will follow a program consisting only of resistance exercise. The intervention will be composed of a different duration and frequency for each type of exercise but with moderate intensity for both groups.

The intervention was planned pursuant to studies and guidelines from the American Sports Medicine Association (ACSM) in respect of exercise and prescription, the American Society of Cardiology (AHA), and in accordance with the recommendations of the World Health Organization (WHO) for physical activity in older adults [4,14,56,57,58,59,60,61,62].

Physiotherapists delivering the exercise intervention will receive two days of program-specific training by the principal investigator physiotherapist prior to the start of the program.

During the intervention period, patients belonging to both intervention groups will not be allowed to participate in any other exercise program. At the same time, patients in the control group will not be allowed to participate in any other form of intervention (exercise program) other than that provided in routine care.

Caregivers will have an essential role in supervising exercise sessions to ensure adherence to guidelines. Caregivers will receive training for this role. Caregiver supervision will include both walking with the participant and supervision of resistance exercise to be performed at home as well as supervision of diary keeping. The intervention will include:

**Intervention Group A:** Combined aerobic and resistance exercise program.

Aerobic Exercise: The type of aerobic exercise in the present study will involve walking at moderate intensity. Walking is the primary mode of physical activity, given its widespread popularity and ease of administration to a broad segment of the elderly population [63]. We focus on moderate training, as studies indicate the greatest effects compared to light or vigorous exercise [64]. The frequency of aerobic exercise will amount to 30 min, 5 days per week. Moderate intensity is defined as 64–76% of the HRmax which is the most commonly used indicator for determining the intensity of aerobic exercise [4,11,56]. The maximum heart rate is calculated according to the type: HRmax = 220 − age.

Moderate intensity control will be monitored based on the participant’s Borg scale of subjective perception of fatigue during exercise by the caregiver at home. Specifically, exercise intensity is graded using a 6–20 category ratio scale (Borg Rating of Perceived Exertion (BRPE) Scale 6–20) according to fatigue and breathlessness. Medium volume is set to approximately 13 [56,65,66]. Caregivers will supervise all exercise sessions since these take place at home, whilst the sessions will be monitored by physiotherapists once a week for the first 2 weeks and subsequently once a month.

Resistance Exercise: The resistance exercise in the study will target the major muscle groups of the body and will be performed with limb weights at moderate intensity according to 50–69% of a maximum repetition (% 1-RM) [56]. The intervention will include 2 sets of 10 exercises of the main muscle groups starting with 8 repetitions which will progressively be increased to 12 repetitions. The frequency of resistance training will amount to three workouts per week (every 48 h), with a duration of 40–45 min per session, with a break of 1–3 min between sets [56,60,61,62,67,68]. Of the three exercise sessions, two will take place at the recruitment center under the supervision of the physiotherapist and one at home under the supervision of the caregiver. The moderate intensity control will additionally be monitored based on the scale Borg (Rating of Perceived Exertion). During the first two weeks, the physiotherapists will supervise the exercise at home once a week and subsequently once a month.

**Intervention group B:** Resistance exercise program

Intervention group B will perform the same resistance exercise program as intervention group A.

The aerobic exercise program and the resistance exercise program will both be followed progressively. Both intervention programs will also include warm-up and cool-down exercises lasting 5–10 min, respectively, with active exercises for the head, limbs, and torso, as well as stretching.

The interventions were selected and designed so as to provide the possibility of easy reproduction at home, promoting an active lifestyle which could be maintained even after the end of the study. Furthermore, the intervention program including illustrated instructions will be made available to the participants and must be followed for 12 weeks.

Strategies for monitoring and adhering to the intervention will comprise one (1) experienced physiotherapist’s visit to the patient’s home during the first two (2) weeks and then one (1) visit per month, one (1) phone call once a week during the first month, and then one (1) phone call per month. Participants and their caregivers will complete an exercise diary form.

Home visits and telephone communications are intended firstly to ensure that the exercises are performed correctly and safely according to the protocol, secondly to resolve any problems, and thirdly to encourage the participant’s effort.

**Control group C:** No participation in any exercise program

The control group participants will be encouraged to maintain their usual daily activity without engaging in any exercise program. Team members who deviate from their daily routine by following any physical exercise program will be excluded from the team.

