### 2.4. Randomization and Blinding

The randomization will be performed by an independent researcher, who will remain hidden from the rest of the research team involved in the interventions, the assessments, the collection of outcome measurements, and the analysis of data. Prior to the baseline assessment, the participants are to be randomly assigned to one of three groups, A, B, and C (two exercise intervention groups and one usual care—control group), by using random number generator. The allocation sequence will be concealed from the researchers related to the study and the intervention will be assigned using sealed envelopes based on order of recruitment. The random allocation will not appear on the assessment forms and the participants’ names will be replaced by code numbers. 

All participants will be assessed by means of two evaluations prior to the start of the intervention and immediately after the completion of the program (12 weeks) with an optional 12-week extension. Professionals participating in the intervention program will not participate in the physical assessment.

During the assessment, in addition to the demographic data, the following data will be collected: somatometric characteristics (height–weight–body mass index), medication, serious illnesses, any incidents involving falling during the last six months, arterial pressure, heart pulses, oxygen saturation, smoking habits, and level of education. Demographics will only be recorded during the initial assessment.

During each assessment, participants and examiners are not allowed to provide or request any information regarding the exercise program being performed. Furthermore, the assessors will be blinded to previous test results. All the above will be included in the study flowchart (Figure 1) in accordance with the CONSORT guidelines.

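### The stated exclusion of control participants who take up exercise acts after randomisation and has no stated counterpart in arms A and B, so it can bias both exercise-versus-control comparisons

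*Protocol article*

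**What the plan says.** Under the control group C heading, section 4 of the protocol article states: "The control group participants will be encouraged to maintain their usual daily activity without engaging in any exercise program". The next sentence gives the consequence: "Team members who deviate from their daily routine by following any physical exercise program will be excluded from the team". In that position, "team" is most naturally the control group.

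On timing, section 2.4 says: "Prior to the baseline assessment, the participants are to be randomly assigned to one of three groups, A, B, and C". The exclusion can therefore only act on people who have already been randomised.

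For the exercise arms, section 4 says that "patients belonging to both intervention groups will not be allowed to participate in any other exercise program", but attaches no exclusion to a breach. For controls, the same part of section 4 says that they "will not be allowed to participate in any other form of intervention (exercise program) other than that provided in routine care".

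Section 5 compares the three groups at 12 weeks by ANOVA or Kruskal–Wallis, and by ANCOVA on the post-test score with the pre-test score as covariate and group, including control, as the factor. Section 3 lists among the secondary aims "the effect of exercise on physical activity by using the International Physical Activity Questionnaire (IPA-Q) short edition".

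**The concern.** A versus C and B versus C answer whether exercise works, and their validity rests on comparing everyone who was randomised. A rule that drops controls for behaviour during follow-up leaves a self-selected control arm. If uptake of exercise is related to how people would have scored at 12 weeks, the remaining controls no longer stand for the arm that was randomised.

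The link is closest for IPAQ, because being active is both the trigger for exclusion and something the trial measures. For cognition, fitness, balance and mood it is a reasonable inference: motivation, fitness and caregiver support may drive both uptake and outcome. If the excluded controls are not assessed at 12 weeks, the data needed to repair the comparison cannot be recovered. The exclusions also reduce the control arm, and section 2.2 mentions no allowance for losses.

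**Working it through.** **1. The plan's own sample size.** Inputs from section 2.2: three groups, alpha 0.05, power 80%, f = 0.23–0.24. For a one-way ANOVA, the noncentrality is λ = N·f² with (2, N − 3) degrees of freedom.
- f = 0.24, N = 171: λ = 171 × 0.0576 = 9.85, power 0.802.
- f = 0.23, N = 186: λ = 186 × 0.0529 = 9.84, power 0.802.

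The stated 171–186 in total (57–62 per group) reproduces. It holds only if all randomised participants contribute.

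**2. Which removal rules are stated.**

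| Arm | Restriction on other exercise | Stated removal for breach |
|---|---|---|
| A, B | Other programmes barred | None |
| C | None beyond routine care | Exclusion |

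**3. Illustrative bias.** The documents give neither the rate of uptake among controls nor its relation to outcome, so both inputs are assumed. Let a share p of controls be excluded, and let them be d SD better than the remaining controls on the 12-week outcome. The mean of all controls then exceeds the mean of the remaining controls by p × d, which is the bias in each exercise-versus-control contrast.
- p = 5%, d = 0.3: 0.05 × 0.3 = 0.015 SD.
- p = 5%, d = 0.8: 0.04 SD.
- p = 20%, d = 0.5: 0.10 SD.
- p = 20%, d = 0.8: 0.16 SD.

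**4. Unadjusted pairwise type I error,** with 60 per arm before exclusion. The standard error is √(1/60 + 1/(60(1 − p))), the shift is p·d divided by it, and the two-sided 5% error uses a normal approximation.

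| p | d | Standard error | Shift | Error |
|---|---|---|---|---|
| 5% | 0.3 | 0.185 | 0.08 | 5.1% |
| 5% | 0.8 | 0.185 | 0.22 | 5.5% |
| 10% | 0.3 | 0.188 | 0.16 | 5.3% |
| 20% | 0.5 | 0.194 | 0.52 | 8.1% |
| 20% | 0.8 | 0.194 | 0.83 | 13.1% |

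If d is negative (uptake prompted by decline), the bias has the same size and the opposite sign. If d = 0 there is none.

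**5. Effect of the planned adjustments.**
- *ANCOVA.* Assume the 0.8 SD advantage is equally present at baseline and the pre/post correlation is 0.7. The advantage left after adjustment is 0.8 × (1 − 0.7) = 0.24 SD, and the residual SD is √(1 − 0.49) = 0.714. At p = 20% the bias is 0.20 × 0.24 / 0.714 = 0.067 residual SD, the shift is 0.067 / 0.194 = 0.35, and the error is 6.4% instead of 13.1%. Selection that baseline does not capture stays in full.
- *Bonferroni.* At 0.05/3 = 1.67%, the unadjusted error runs from 1.7% (p = 5%, d = 0.3) to 5.9% (p = 20%, d = 0.8).

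**6. Control numbers and power.** From 60 controls, 5–20% exclusion loses 3–12. Starting from 62 per group with f = 0.23, omnibus power falls from 0.80 to 0.77–0.78 at 10% exclusion and 0.73–0.75 at 20%, depending on the pattern of group means.

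**The case against.** The best defence is that the article is condensed and that several stronger charges a reader might draw from it are not supported.

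- *Excluded controls leave the trial and its analysis.* The text speaks only of exclusion from the team. Removal from the group is the natural meaning, but loss of the 12-week assessment is not written. Nor is its retention, and that is the gap.
- *Non-adherent exercise participants are kept.* No section says so. Section 4 is silent on the consequence of a breach in A or B, so the asymmetry is one of stated rules only.
- *The exercise arms are analysed as completers.* The phrase "after the subjects had completed the 12 weeks intervention of the two different exercise programs" belongs to the within-group paired tests and may simply mark the time point. It does not define who enters the ANOVA or ANCOVA.
- *Section 4 flatly contradicts itself on routine-care exercise.* The trigger is deviating from daily routine by following a programme, and exercise already part of routine care need not be a deviation. This is an ambiguity, though one worth resolving, since the control arm is also described as taking part in no exercise programme.
- *The rule favours exercise.* That requires exercising controls to have the better prognosis, which no section states.

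The size is also open. The uptake rate is assumed, and the 5–13% range is not the error of the planned test, which uses the pre-test covariate and a Bonferroni correction.

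All of these limits stand. They do not remove the core: a post-randomisation exclusion is written into the plan for one arm, with nothing to say that those participants are still followed or analysed as allocated. An unseen analysis plan might supply an analysis set, but the exclusion rule as stated would still have to be withdrawn or qualified.

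**Conclusion.** The point holds as a risk of bias created by a stated rule. It affects A versus C and B versus C, and leaves A versus B alone. Direction and size cannot be derived from the documents: removing better-prognosis controls would flatter exercise, while removing those who took up exercise because they were declining would do the reverse. The figures of 0.015–0.16 SD and about 5–13% unadjusted pairwise error rest wholly on the assumed 5–20% exclusion and 0.3–0.8 SD advantage. They are smaller where the pre-test score captures the selection, and negligible at the low end. The case for changing the rule rests on principle and on the irrecoverable loss of 12-week data, more than on these numbers.

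**What to change.** Replace the exclusion sentence in section 4 with wording such as: control participants who start an exercise programme remain in the trial, are assessed at 12 weeks and are analysed in the group to which they were randomised; the uptake is recorded as a protocol deviation.

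In section 5, make all randomised participants, as allocated, the main analysis set for every arm. Use a per-protocol set only as a sensitivity analysis, with the same deviation rule in all three arms.

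Separately, reconcile the two parts of section 4 on whether exercise provided in routine care is allowed in the control group.

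The change is to protocol wording, plus the 12-week assessment of controls who would otherwise have been dropped. The price is that contamination slightly dilutes the estimated exercise effect.
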